### Plans to give access to the full protocol, participant level-data and statistical code {31c}

The trial protocol, evaluation indicators, and analysis plan will be registered and published prior to the commencement of data analysis. The data generated and analyzed for this study will be deidentified and, after study completion and publication, can be made available upon reasonable request to the PI ([name]) and subsequent approval by the project management partner, Impact and Innovations Development Centre (IIDC). Access to the data will be granted for research purposes only.

### Composition of the data monitoring committee, its role and reporting structure {21a}

A formal Data Monitoring Committee (DMC) will not be established for this trial. The study involves a low-risk educational intervention delivered via trained community-based mentors, and there is no anticipated serious harm or adverse effect. Given the low-risk nature of the intervention, the research team has determined that a DMC is not necessary. Instead, the PI and co-Is will work in close collaboration to monitor data collection and trial progression, ensuring adherence to the protocol. Weekly meetings with the research and program team will be established to ensure regular communication on progress. Any deviations from the protocol will be documented and reported.

### Adverse event reporting and harms {22}

The study involves an informal educational intervention for fathers and mothers in Uganda whose eldest biological child is below the age of three years. The intervention is considered low-risk with no anticipated adverse events stemming directly from the intervention. However, it is expected that study enumerators and implementation teams at each study site may identify individuals at risk of or those who are currently experiencing violence and maltreatment. The research and implementing teams are equipped with monitoring tools to document referrals to the nearest health facility or responsible institution and the reasons for referral. These include the following: Child Protection Services through the Child Wellbeing Committees which address cases of child abuse, neglect, and exploitation; Gender-Based Violence (GBV) Prevention and Response through community GBV committees, one-stop centers for survivors, and legal aid services to support GBV survivors; and Social Welfare and Safeguarding services for vulnerable groups such as orphans, elderly persons, and people with disabilities, ensuring they have access to financial and practical assistance.

In the event that a serious adverse event occurs due to the study and intervention, any/all serious adverse events will be reported promptly to the National Council for Science and Technology (UNCST) after ethical review and approval from Makerere University School of Social Sciences Research and Ethics Committee (designated research and ethics committee). Unanticipated problems involving risks to research participants or others will be reported promptly to the UNCST. New information that becomes available which could change the risk/benefit ratio to participants will also be submitted promptly for UNCST notification.

### Frequency and plans for auditing trial conduct {23}

The ethical committees responsible for approval can spontaneously audit trial conduct, independently of investigators and the sponsor.

### Plans for communicating important protocol amendments to relevant parties (e.g., trial participants, ethical committees) {25}

In case of substantial protocol modifications, these will be reported immediately to the following scientific ethics bodies which will review and approve the changes: Makerere University School of Social Science Research and Ethics Committee; Uganda National Council for Science and Technology (UNCST); and University of California San Diego Institutional Review Board. All potential modifications will be tracked and dated.

## Dissemination plans {31a}

Anonymized data will be analyzed, and all results regardless of outcome will be made available by publication in peer-reviewed international journals and presentation at international scientific conferences. In addition, the REAL Fathers Consortium of researchers, implementers, and policymakers will generate on an ongoing basis short briefs and PowerPoint presentations and will ensure findings from baseline, endline, and follow-up are shared with implementing partners and community members; local, regional, and national policymakers; and global public health practitioners.

## Discussion

This phased rollout cluster randomized controlled trial will be the first study of its kind to evaluate the effectiveness of the REAL Fathers intervention, a community-based, gender norms transformative parenting program in six regions of Uganda. We include a large, representative cohort of young fathers and their female partners with children under the age of three across six diverse regions in Uganda. The trial will expand the evidence base on programming that integrates prevention of violence against children and intimate partner violence, alongside the promotion of increased father-child engagement via social support for changes in caregiving norms within families [28]. The trial will measure various outcomes from both fathers and mothers, which were chosen to reflect important aspects of the program theory of change and policy priorities in Uganda. The trial’s primary outcomes are as follows: (1) reduced intimate partner violence; (2) reduced violent discipline of children; (3) increased father-child engagement and play; (4) improved early childhood development. In particular, despite being recognized as a global priority, the impact of violence prevention programs on early child development outcomes has rarely been examined [56]. Given that the earliest years of life are foundational for children’s later life health and wellbeing, understanding the links between family violence, parenting, and early childhood development has significant implications for policy and programming (see, e.g., [36, 57]).

The trial is also powered to stratify analyses by region with the aim of providing policymakers and program implementers more granular information on which to base regional-level programming and policies in response to differentials in socio-cultural norms by geographic region. The trial will also examine additional questions of for whom the intervention works by testing for interaction by age of the young father, duration of time living with a female partner, age and sex of the child, alcohol consumption, and education level of the father and female partner. These outcome data will be complemented by extensive routine monitoring data collected by implementing partners throughout the project cycle to assess fidelity, refine training and delivery, and strengthen implementation quality to maximize effectiveness in achieving the intended outcomes along the theory of change. In addition to generating evidence on ‘what works’ and ‘for whom’ in prevention programming, data generated from this longitudinal cRCT will also allow, for the first time, an examination of household-level violent child discipline and IPV initiated by both male and female partners. This expands the evidence base on heterosexual IPV, which typically focuses on men as perpetrators and women as victims.

This multi-region design and large cohort of couple-dyads enables a rigorous evaluation in a cRCT to measure the effectiveness of the REAL Fathers intervention. The cRCT design and progressive rollout across multiple cohorts will allow for timely adaptations to the program model based on emerging experiences and lessons learned as it scales out to more communities. Findings from this trial will inform future research and programs designed to address intergenerational cycles of violence that impede healthy child development. Our research team will partner with an advisory committee of ministry stakeholders to ensure policy relevance in the national and regional Ugandan policy space to promote sustainability and scale. Ultimately, this study will contribute valuable evidence on how this social and behavior change intervention reduces rates of violence against children, intimate partner violence, and improving child and family wellbeing, while providing an opportunity to investigate the clustering of multiple forms of violence within the household context and their connections to early childhood development.

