### Sample size {14}

Sample size is based on calculations using the outcome measure of proportion of young fathers who apply positive parenting behaviors. Based on the pilot studies on REAL Fathers intervention in Uganda, and to ensure sufficient statistical power of sub-group analyses at the regional level to obtain the largest sample size necessary, we assume only 40% of the young fathers use positive parenting skills at baseline [40]. From pilot studies, the REAL Fathers intervention should improve this proportion by at least 10% (effect size on absolute scale) by the endline [40]. The sample size computation is based on the formula:$$n=\frac{[2*{\left({Z}_{\alpha /4}+{Z}_{1-\beta }\right)}^{2}*\overline{P }(1-\overline{P })]}{{({P}_{1}-{P}_{0})}^{2}}\times Deff$$where:

*n* = minimum sample size of individuals required per arm of study

*Z*_α/4_ = the critical value of the standard normal variate at significance level of α/4 (*α* is assumed to be 0.05 or 95% certainty for improvement in the four primary outcome indicators). By setting the critical *Z* value corresponding to an alpha level of 0.0125 (i.e., α/4), our sample size calculation adjusts for multiple outcome testing while maintaining an overall 5% level of statistical significance for the trial.

*Z*_1-β_ = the critical value of the standard normal distribution at a power of 1-β (assumed to be 0.80 or 80% power)

*P*_0_ = the value of positive parenting indicator at the baseline; assumed 40%

*P*_1_ = the value of positive parenting indicator at the endline; assumed to be 50%—a 10-percentage point increase based on pilot studies$$\overline{P } = \frac{{P}_{1}+{P}_{0}}{2}$$

*Deff* = clustering effect, assumed to be 2.3

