Based on the Uganda Bureau of Statistics 2019 population projections and Uganda Demographic and Health Survey 2016 data, only 4% of the male population (16–25 years) are young fathers who are married or cohabiting [6]. According to the latest Uganda population and housing census, the average village size is about 100 households [49]. Thus, no more than 10 young men (16–25 years) will be fathers whose eldest child is below the age of three years. To be on the conservative side, we assume that, on average, only 8 young fathers are eligible for the study from any given village. Let $$\overline{m }$$ denote this average and suppose *cv* is the coefficient of variation in the number of fathers across the different villages, and ρ is intra-cluster correlation (ICC). Pilot studies on the REAL Fathers intervention approximated ICC of 0.20–0.24 at the village level. Thus:$$Deff=\left(1+\left(\left({cv}^{2}+1\right)\overline{m }-1\right)\rho \right)=\left(1+\left(\left(0.063+1\right)\times 7-1\right)\right)\times 0.20=2.3$$

Based on the above parameters and an attrition rate of 10% between the baseline and endline, a total of 1872 couple dyads is required per study arm (3744 in total). This translates to 156 couples per district: 78 in each study arm from 6 villages; and 312 couples per geographical region. This makes an assumption of treatment effect size of 10% on indicators at project level and 80% statistical power and 95% certainty (alpha = 0.05).

The study is being conducted across regions characterized by diverse subcultures, both between and within locations. To ensure sufficient power to detect potential heterogeneity in treatment effects across key subcultural groups, we adjusted the sample size accordingly. Drawing on pilot data, we anticipate a moderate level of effect heterogeneity across these subcultures. According to Ford and Norrie (2016) [50] and Kent et al. (2018) [51], moderate heterogeneity corresponds to a coefficient of variation (CV) of approximately 20% in treatment effects. To account for this, we increased the originally planned sample size by 20%, resulting in a target of 2200 participants per study arm.

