### Methods for additional analyses (e.g., subgroup analyses) {20b}

For each trial cohort (i.e., data collection cohorts), hierarchical random effects models will be estimated to understand variation or treatment effects heterogeneity at the regional- and sub-county levels. After the full data collection is complete (i.e., after data collection on all three trial cohorts is completed), stratified analyses by region will be conducted to provide policymakers and program implementers more detailed information on intervention effects given hypothesized differentials in socio-cultural norms by geographic region. When assessing outcomes at a regional level, the index indicators will be estimated within 10% precision. In addition, we will conduct exploratory sub-group analyses on key covariates including the following: age of the young father, duration of time living with spouse/partner, age and sex of the child, alcohol consumption, and education level of father and spouse/partner.

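### Power for regional effects and for effect heterogeneity is claimed, but the sample size delivers 80% power only at project level

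*Protocol article*

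**What the plan says.** Three places in the protocol article claim power below project level.

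- Discussion: "The trial is also powered to stratify analyses by region", with the stated purpose of informing regional programming and policy.
- Sample size {14}, opening paragraph: the baseline proportion is chosen partly "to ensure sufficient statistical power of sub-group analyses at the regional level".
- Sample size {14}, closing paragraph: "To ensure sufficient power to detect potential heterogeneity in treatment effects across key subcultural groups, we adjusted the sample size accordingly". The adjustment adds 20% because the treatment effect is expected to vary with a coefficient of variation of about 20%. The resulting target is 2,200 per arm.

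The calculation itself is set at a different level: "This makes an assumption of treatment effect size of 10% on indicators at project level and 80% statistical power and 95% certainty". No power figure for a region, or for an interaction, is printed anywhere.

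The section on additional analyses {20b} plans region-stratified analyses once all cohorts are complete. It says regional indicators will be estimated to within 10%. For each cohort, "hierarchical random effects models will be estimated to understand variation or treatment effects heterogeneity at the regional- and sub-county levels".

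**The concern.** Power at project level does not carry over to each of six regions, which hold one sixth of the sample each. An allowance of 20% does not close a gap of that size. The protocol nevertheless presents regional and heterogeneity power as achieved properties of the design, and it directs the regional results to policymakers.

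Suppose the programme really gave 10 points in every region. At alpha 0.05 about 6 x (1 - 0.35) = 3.9 regions would be expected to miss significance. A reader told that the trial was powered by region could take those results as evidence of no benefit there, or take chance differences between regions as cultural ones.

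**Working it through.** **Inputs, all from Sample size {14} unless noted**

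- Proportions 0.40 and 0.50 ("the value of positive parenting indicator at the baseline; assumed 40" per cent, plus 10 points), so the mean proportion is 0.45 and 0.45 x 0.55 = 0.2475.
- Power "assumed to be 0.80 or 80% power". The critical value is described as "corresponding to an alpha level of 0.0125 (i.e., α/4"). Sidedness is not stated; two-sided values are used here (z = 1.960 for 0.05 and 2.498 for 0.0125).
- Design effect 2.3, attrition 10%.
- 78 couples per arm per district and four districts per region (Study setting {9}), so 78 x 4 = 312 per arm per region. The section prints 312 per geographical region, which fits 156 couples per district only as a per-arm figure, since 156 x 4 = 624.
- Four sub-counties per arm per region (Sequence generation {16a}: two per district, one to each arm).

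**The plan's own figure**

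n per arm = 2(z + 0.842)^2 x 0.2475 / 0.10^2 x 2.3 / 0.9 gives 1,411 at two-sided 0.0125, 1,202 at one-sided 0.0125 and 993 at two-sided 0.05. The printed 1,872 is not reproduced. That is a separate matter: 1,872 per arm gives about 91% power at 0.0125 and 97% at 0.05 for the whole project. The same formula applied within one region therefore asks for 993 to 1,411 per arm, against 312 planned.

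**One region, endline comparison**

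SE = sqrt(2 x 0.2475 x 2.3 / (312 x 0.9)) = 0.0637. Power = Phi(0.10/SE - z).

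| Per arm per region | SE | Power, 0.05 | Power, 0.0125 |
|---|---|---|---|
| 312 (1,872 per arm) | 6.4 points | 35% | 18% |
| 367 (2,200 per arm) | 5.9 points | 40% | 21% |
| 312, t on 4 + 4 - 2 = 6 df | 6.4 points | 26% | 10% |

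At 312 per arm, the effect detectable with 80% power is (1.960 + 0.842) x 6.37 = 17.8 points, or (2.498 + 0.842) x 6.37 = 21.3 points. One-sided testing gives 47% (0.05) or 25% (0.0125).

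If 78 couples come from 6 villages, that is 13 per village. The design effect is then 1 + (1.063 x 13 - 1) x 0.20 = 3.56, and power falls to 24% and 11%.

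**Difference-in-differences**

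The within-person correlation r is not given, so a range is assumed, keeping the design effect at 2.3 for change. SE becomes 0.0637 x sqrt(2(1 - r)).

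| r (assumed) | SE | Power, 0.05 | Power, 0.0125 |
|---|---|---|---|
| 0 | 9.0 points | 20% | 8% |
| 0.5 | 6.4 points | 35% | 18% |
| 0.8 | 4.0 points | 70% | 49% |

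At 367 per arm and r = 0.8, SE is 0.0587 x sqrt(0.4) = 0.0371 and power is 77% and 58%.

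**Regional precision**

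- One arm's prevalence: 1.96 x sqrt(0.2475 x 2.3 / 280.8) = 8.8 points, inside 10.
- Between-arm difference: 1.96 x 6.37 = 12.5 points (2.447 x 6.37 = 15.6 with t on 6 df), outside 10. At 367 per arm it is 11.5 points.

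**Heterogeneity**

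A coefficient of variation of 20% on a 10-point effect is a standard deviation of 2 points. The protocol names no test and no number of groups. Assume a 5-df chi-square test across the six regions at alpha 0.05. The noncentrality is 5 or 6 (by convention) x 0.02^2 / 0.0637^2 = 0.49 to 0.59, and power is 7.3-7.7%. At 2,200 per arm it is 7.7-8.3%. With 2 to 12 equal groups instead, power runs from about 7% to 13%.

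**The case against.** - **Precision, not power, is the regional target.** The 10% criterion in {20b} is the only numerical regional target, and it is met for one arm's prevalence. This stands, but it says nothing about a treatment effect, whose interval is wider.
- **The planned model may do better than an endline comparison.** True, and no single power figure should be treated as firm. Yet r up to 0.8 leaves power below 80% at either sample size.
- **Trial design {8} can be read as 1,872 per arm in every cohort.** That would give 936 per arm per region and 59-78% power. It contradicts the total of 3,744 in the same sentence, and with the stated attrition the endline calculation still falls short of 80%.
- **The 0.0125 level may not apply to regional strata.** The multiplicity correction is written for the primary outcomes only. The 0.05 figures then apply, and they are still 35-40%.
- **A hierarchical model is already planned and no regional significance rule is set.** Correct. The fault lies in the claims made for the design; the misreading by region is a risk, not a planned decision rule.

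A reader might also infer that sub-county modelling is impossible and should be dropped. The protocol does not support that. With repeated measures, variation between sub-counties in change can be estimated. What cannot be separated without further assumptions is a sub-county's own treatment effect from its ordinary change over time, since each sub-county is wholly in one arm.

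**Conclusion.** The claims of power for regional effects and for heterogeneity are not supported by the calculation shown. Regional power for the planned 10 points is about 35% (alpha 0.05) or 18% (0.0125) with 312 per arm, and 40% or 21% at the 2,200 target. Under difference-in-differences with 312 per arm it ranges from 8% to 70% for assumed r of 0 to 0.8. These figures rest on the plan's proportions, its village-level design effect and its attrition.

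The 7-8% for heterogeneity is conditional on a six-region test that the protocol does not specify, and should be quoted only with that condition. The conclusion that a 20% increase does not secure heterogeneity power holds across the 2 to 12 groups tried. Recruitment {15} moreover still aims for 1,872 per arm.

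It would be wrong to infer that the trial as a whole is underpowered. On the stated inputs, project-level power is 91-97%.

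**What to change.** 1. Withdraw the statements of regional power in the opening of Sample size {14} and in the Discussion. Withdraw also the heterogeneity-power rationale for the 20% increase at the end of Sample size {14}.
2. State the expected regional power, with its assumptions, and the expected 95% half-width of a regional between-arm difference (about 12 points, or about 16 with t on 6 df). Say that the 10% precision in {20b} refers to one arm's prevalence.
3. Make the hierarchical model already planned the main source of regional conclusions: one pooled model with a treatment-by-region term and partially pooled regional estimates with confidence intervals. Keep the region-stratified results, labelled exploratory.
4. In {20b}, describe the sub-county random effects as variation in change between sub-counties, not as sub-county treatment effects.

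The cost is wording and a clear order of precedence among analyses already planned. No new data are needed and the primary analysis does not change. The price is that a stated property of the design becomes less favourable.

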## Trial status

The protocol is version 1.2 of December 10, 2024. The trial was initiated in November 2023 and recruitment is expected to be complete in December 2025. Enrolment is active at the time of submission.

## Data Availability

After study completion and publication, the trial dataset can be delivered upon reasonable request to the PI ([name]) and subsequent approval by the project management partner, Impact and Innovations Development Centre (IIDC). Access to the data will be granted for research purposes only.

## Appendix

## Abbreviations

Co-I: Co-Investigator
cRCT: Cluster randomized controlled trial
DID: Differences-in-differences
DMC: Data Monitoring Committee
ECD: Early childhood development
FS: Field Supervisor
GEH: Center on Gender Equity and Health at the University of California San Diego
ICC: Intra-cluster correlation
IP: Implementing partner
IPV: Intimate partner violence
ITT: Intention-to-treat
LCI: Local Council 1
M&E: Monitoring and evaluation
MIS: Monitoring Information System
PI: Principal Investigator
RA: Research Assistant
REAL Fathers: Responsible, Engaged and Loving Fathers
SoP booklet: Standard Operating Procedures booklet
UNCST: Uganda National Council for Science and Technology
VAC: Violence against children
VHT: Village Health Team
VSLA: Village Savings and Loan Association
